Mindfulness is a unique attentional ability developed through meditation practice, characterized by present-moment focus and nonjudgmental attitude. Mindfulness training is used to alleviate emotional problems and improve the quality of life in a variety of clinical groups. Previous studies have shown that mindfulness reduces stress, depression, and anxiety, and improves wellbeing (17–22). Furthermore, mindfulness training can improve workers’ mental health and job performance. According to previous studies, mindfulness reduces workers’ stress and burnout (23–26) and improves work engagement and job performance (27–29).

Because of these benefits, mindfulness has recently become a core component of several smartphone-based healthcare applications, such as Headspace and Calm. Previous studies have shown that mobile mindfulness training (MMT) reduces users’ stress, depression, and anxiety, and improves their quality of life (16, 30–33). However, most studies on the effects of mobile mindfulness training have been conducted on students or the general public, with relatively few studies targeting workers (16). Moreover, according to previous research (34), more than half of digital mindfulness-based intervention studies have been conducted with healthcare workers, while less than one-fifth of the studies have been conducted with office workers. Therefore, this study will investigate the effects of MMT on office workers’ stress, burnout, and work engagement.

This study aims to verify the effectiveness of MMT on the mental health of office workers and explore its mechanisms. The primary objective of this study is to investigate whether a four-week MMT improves office workers’ mental health, stress, burnout, and work engagement. The results of this study are predicted as follows: (i) The experimental group will exhibit reduced burnout compared to the control group after 4 weeks. (ii) The experimental group will exhibit enhanced work engagement compared to the control group after 4 weeks. (iii) The experimental group will exhibit lower perceived stress compared to the control group after 4 weeks. (iv) The experimental group will exhibit increased mindfulness compared to the control group after 4 weeks. (v) The experimental group will exhibit superior subjective vitality compared to the control group after 4 weeks.

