### Sample size

2.6

The minimum sample size was calculated using the G* Power program (35). A value of 0.15 indicating a small effect size and a significance level of 0.05 were set, and the power was applied as 0.80. The calculation indicated that a minimum of 90 participants is required, with a minimum of 45 participants per group. Considering a dropout rate of 20%, a maximum of 57 participants per group and a total of 114 participants will be recruited.

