#### Maslach burnout inventory—general survey (MBI-GS)

2.10.1

The Korean version of the MBI-GS will be used to assess burnout (36). This scale consists of 5 items for burnout, 4 items for cynicism, and 6 items for decreased job efficacy. Decreased job efficacy is reverse scored. The MBI-GS is a self-reported 5-point Likert scale. Each item ranges from 1 to 5. The total score ranges from 15 to 75. A higher score indicates more severe burnout. In a previous study (36), Cronbach’s alpha was 0.90 for burnout, 0.81 for cynicism, and 0.86 for decreased job efficacy.

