#### The Utrecht work engagement scale (UWES)

2.10.2

The Korean version of the UWES will be used to assess work engagement (37). This scale consists of 3 items for vigor, 3 items for dedication, and 3 items for absorption. The UWES scale is a self-reported 7-point Likert scale. Each item ranges from 0 to 6. The total score ranges from 0 to 54. A higher score indicates more immersion in one’s job. In previous studies (37), Cronbach’s alpha was 0.91 for vigor, 0.89 for dedication, and 0.90 for absorption.

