### Statistical analyses

2.13

Analyses will be conducted according to the Intention-To-Treat (ITT) principle, and missing data will be imputed using the expectation maximization algorithm.

First, to investigate the effectiveness of MMT, a 2 (group: experimental vs. control) × 2 (survey time: T1 vs. T2) repeated-measures ANOVA will be performed for MBI-GS, UWES, PSS, CMAS-R, and IVS. If the interaction between the group and survey time is significant, a simple main effect analysis will be performed. Second, a paired *t-*test will be performed on MBI-GS, UWES, PSS, CMAS-R, and IVS in the experimental group to examine the follow-up effect of MMT. Third, a subgroup analysis will be performed to investigate the difference in effectiveness depending on the amount of application usage. For this purpose, 2 (subgroup: high-usage vs. low-usage) × 2 (survey time: baseline vs. post-intervention) repeated-measures ANOVA will be performed. Data from both the experimental and control groups will be used for subgroup analysis. If the interaction between the subgroup and survey time is significant, a simple main effect analysis will be performed. Fourth, a mediating effect analysis will be performed to investigate whether mindfulness and subjective vitality mediate the relationship between application use and burnout or work engagement.

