## Discussion

3

This study aims to investigate the effects of MMT on office workers. This study is designed as a two-armed randomized controlled trial and will primarily investigate the effects of MMT on perceived stress, burnout, work engagement, mindfulness, and subjective vitality. Additionally, this study will investigate the follow-up effect of MMT and perform subgroup analysis to compare differences in effectiveness depending on application usage. Finally, this study will investigate whether mindfulness and subjective vitality mediate the relationship between MMT and burnout or work engagement.

MMT will improve the mental health and productivity of office workers. According to previous studies, mindfulness training reduced perceived stress (16) and increased mindfulness and subjective vitality (41, 42). Mindfulness training reduced job burnout and increased job engagement among health care providers (25, 43). Furthermore, the positive effects of MMT will be maintained even after completing the intervention. According to a meta-analysis study, the follow-up effect of mindfulness meditation on anxiety and stress was found to be significant (16). These results suggest that MMT improves the mental health and productivity of office workers, and that the improved effects can be maintained even after training ends.

The amount of application usage will affect the effectiveness of MMT. According to previous research, as the number of sessions of mindfulness training increased, stress significantly decreased (44). According to a study that examined the effects of mindfulness training on a weekly basis (45), the level of mindfulness significantly increased after 2 weeks of training, and perceived stress significantly decreased after 4 weeks of training. These findings suggest that the effectiveness of MMT may also increase as the amount of application usage increases.

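### Two primary outcomes share one 0.05 level with no order or success rule, so the stated 0.05 and 80% power do not both hold for the pair

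*Protocol article*

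**What the plan says.** Section 2.10, headed as primary outcomes, contains two scales. Section 2.10.1 opens "The Korean version of the MBI-GS will be used to assess burnout (36" and section 2.10.2 opens "The Korean version of the UWES will be used to assess work engagement (37". Section 2.11 lists PSS, CAMS-R and IVS as secondary.

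Section 2.13 treats all five scales alike. A 2 (group) × 2 (T1, T2) "repeated-measures ANOVA will be performed for MBI-GS, UWES, PSS, CMAS-R, and IVS", and a significant interaction leads to a simple main effect analysis. It gives no test level, no order and no rule for combining the two primary results.

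Section 2.6 holds the only significance level in the article: "a significance level of 0.05 were set, and the power was applied as 0.80". With an effect size of 0.15 this gives at least 90 participants (45 per group), raised to 114 (57 per group) for 20% dropout.

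The wording around the outcomes is looser than the headings. The primary objective in the Introduction carries five separate hypotheses, one per scale, down to "v) The experimental group will exhibit superior subjective vitality compared to the control group after 4 weeks". The Discussion says the trial "will primarily investigate the effects of MMT on perceived stress, burnout, work engagement, mindfulness, and subjective vitality".

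**The concern.** A trial with two primary outcomes needs one further sentence: does it succeed if either outcome is significant, only if both are, or in a stated order? The answer decides what the type I error and the power are. The article leaves it open while fixing a sample size that fits one test at the full 0.05.

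This matters at the analysis stage. If one of MBI-GS and UWES is significant and the other is not, the plan does not say whether efficacy has been shown. Claiming it on the significant one is then a choice made after seeing the data, with an error rate above the level used in the design.

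**Working it through.** **Inputs.** From section 2.6: effect size 0.15 (metric not named), level 0.05, power 0.80, 90 evaluable, 20% dropout. From section 2.13: two groups, two time points, interaction test. Assumed, because the article gives neither: the correlation ρ between repeated measures, and the correlation r between the two outcomes' test statistics. For UWES the same effect size as for MBI-GS is assumed. The interaction F test is non-directional, so 0.05 is taken as two-sided.

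**Step 1: reproduce the plan's figure.** Read 0.15 as Cohen's f. For the within-between interaction with m = 2 time points, λ = f² × N × m / (1 − ρ), with 1 and N − 2 degrees of freedom.

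- With ρ = 0.5 and N = 90: λ = 0.0225 × 90 × 2 / 0.5 = 8.1. Power at 0.05 is 0.804, and 90 is the smallest even N that reaches 0.80.
- With ρ = 0.3 the required N is 126; with ρ = 0.7 it is 56. So 90 points to ρ = 0.5.
- Dropout: 45 / 0.80 = 56.25, rounded up to 57 per group, 114 in total, as stated.

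The stated size is therefore that of one interaction test using all of the 0.05.

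**Step 2: either outcome suffices, each at 0.05.** Family-wise error is 1 − P(neither test rejects).

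| r (assumed) | Chance of at least one false positive |
|---|---|
| 0 | 1 − 0.95² = 9.75% |
| 0.5 | about 9.1% |
| 0.7 | about 8.3% |

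The correlated rows come from simulating one million pairs of two-sided z-tests. The upper bound is 0.05 + 0.05 = 10%.

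**Step 3: both must succeed, each at 0.05.** Error is not inflated. Joint power at N = 90 is Φ₂(z, z; r), the bivariate normal probability with z = Φ⁻¹(0.804) ≈ 0.855.

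| r (assumed) | Joint power |
|---|---|
| 0 | 0.804² = 0.646 |
| 0.5 | 0.69 |
| 0.7 | 0.72 |

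It cannot exceed the single-test power of about 0.80.

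**Step 4: possible repairs at N = 90.**

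- *Fixed sequence, MBI-GS then UWES.* Power for MBI-GS stays at 0.804. A UWES claim needs both tests significant, so its power is the joint power of step 3, about 65% to 72%.
- *Bonferroni, 0.025 each.* Power per outcome falls to 0.714. Restoring 80% needs N = 110, or 55 / 0.80 = 68.75, rounded up to 69 per group, 138 recruited.
- *Holm.* The smaller p-value is tested at 0.025 and the other at 0.05 if the first is significant. Power per outcome therefore lies between the Bonferroni 0.714 and the unadjusted 0.804.

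**The case against.** The strongest reply is that the error rates in step 2 depend on a decision rule the article does not contain. The Discussion makes its recommendation conditional on results agreeing with the hypotheses, both in the plural. A reader might infer that any single significant result would be enough; the text does not say so. This stands, and it is why the 8% to 10% is stated only for the either-outcome rule. It does not remove the point, because the both-outcomes rule fails on power instead.

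A second reply is that multiplicity methods are often left to an analysis plan, and that section 2.13 states no level, so testing each outcome at 0.05 is inferred from section 2.6. That is fair. But the naming of two primary outcomes and a sample size that uses the whole 0.05 on one test are fixed in this document. A later adjustment would change the power that section 2.6 states.

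Two stronger readings are tempting. One is that the article contradicts itself on which outcomes are primary. Sections 2.10 and 2.11 rank the scales clearly. The Introduction and Discussion rank questions (effect at four weeks, follow-up, usage, mediation), and a secondary scale may inform the primary question. No passage calls PSS, CAMS-R or IVS a primary outcome, so this is loose wording. The other is that five tests at 0.05 give a family-wise error of 1 − 0.95⁵ = 22.6%. That needs all five scales in one confirmatory family, which the headings exclude.

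**Conclusion.** The point holds for the pair MBI-GS and UWES. Under the either-outcome rule, error is about 8% to 10%, not 5%. Under the both-outcomes rule, error is held at 5% but power is about 65% to 72%, not 80%. Neither rule delivers both figures of section 2.6 for the pair.

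Independence is the high end for error and the low end for joint power. The Introduction describes burnout as the opposite of engagement, so the correlated rows are the more plausible ones, with the sign of r immaterial to the two-sided error rate. The figures rest on f = 0.15 for both outcomes, ρ = 0.5, and r between 0 and 0.7 in size. This should be corrected, but it is not a reason to redesign the trial.

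**What to change.** In section 2.13, state that the confirmatory family is MBI-GS and UWES, tested in the order listed in section 2.10: the MBI-GS interaction at two-sided 0.05, then UWES at two-sided 0.05 only if MBI-GS is significant. If the sponsor does not wish to rank the two, Holm's procedure is equally acceptable.

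In section 2.6, state that the 80% power applies to the first test only and that power to claim UWES is lower. Under Holm, state instead the power per outcome that results.

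Report PSS, CAMS-R and IVS as secondary, with estimates and confidence intervals and no confirmatory claim. Reword the primary objective in the Introduction and the opening of the Discussion so that they match sections 2.10 and 2.11.

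The cost is wording only: recruitment has not started and 114 can stand. The price of the fixed sequence is that UWES cannot be claimed as confirmed if MBI-GS fails; Holm avoids that but gives up some power on MBI-GS.

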The secondary objective of this study is to perform a follow-up examination to assess the effect of MMT on the mental health, stress, burnout, and work engagement of employees over a longer period. The results of this study are predicted as follows: (i) Burnout at follow-up will be lower than that at baseline in the experimental group. (ii) Work engagement at follow-up will be higher than that at baseline in the experimental group. (iii) Perceived stress at follow-up will be lower than that at baseline in the experimental group. (iv) Mindfulness at follow-up will be higher than that at baseline in the experimental group. (v) Subjective vitality at follow-up will be higher than that at baseline in the experimental group.

The third objective of this study is to examine differences in the effectiveness of MMT depending on the amount of application usage. The results of this study are predicted as follows: (i) The high-usage subgroup will exhibit a greater reduction in burnout compared to the low-usage subgroup after MMT. (ii) The high-usage subgroup will exhibit a greater increase in work engagement compared to the low-usage subgroup after MMT. (iii) The high-usage subgroup will exhibit a greater reduction in perceived stress compared to the low-usage subgroup after MMT. (iv) The high-usage subgroup will exhibit a greater increase in mindfulness compared to the low-usage subgroup after MMT. (v) The high-usage subgroup will exhibit a greater increase in subjective vitality compared to the low-usage subgroup after MMT.

The fourth objective of this study is to examine whether mindfulness and subjective vitality mediate the relationship between MMT and burnout or work engagement. The results of this study are predicted as follows: (i) Mindfulness will mediate the relationship between MMT and burnout. (ii) Mindfulness will mediate the relationship between MMT and work engagement. (iii) Subjective vitality will mediate the relationship between MMT and burnout. (iv) Subjective vitality will mediate the relationship between MMT and work engagement.

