#### Inclusion criteria

2.3.1

Office worker over 19 years of age.Participants subjectively complaining of stress related to various issues at work.Participants who can participate in the study for 8 weeks.

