#### Wait-list control

2.4.2

The control group will not receive any intervention for the first 4 weeks. However, for ethical reasons, the control group will be given InMind for the next 4 weeks. The MMT procedures for the control group will be the same as that for the experimental group. The experimental group will not receive any intervention while the control group will perform MMT.

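### The week-8 effect of MMT is tested only by a paired baseline-to-week-8 t-test in the experimental arm, which cannot separate an MMT effect from change that would occur without treatment

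*Protocol article*

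**What the plan says.** The Introduction of the protocol article states the secondary objective as a "follow-up examination to assess the effect of MMT on the mental health, stress, burnout, and work engagement of employees over a longer period". Its five hypotheses are all within-arm. The first reads "Burnout at follow-up will be lower than that at baseline in the experimental group", and the other four follow the same pattern for work engagement, perceived stress, mindfulness and vitality.

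Section 2.13 supplies the test: a paired t-test that "will be performed on MBI-GS, UWES, PSS, CMAS-R, and IVS in the experimental group to examine the follow-up effect of MMT". That sentence does not name the time points; the T3-against-T1 pairing comes from the Introduction. The only between-group analysis in 2.13 is the group-by-time ANOVA on T1 and T2. T3 enters no comparison between arms, although Table 2 schedules every scale at T3.

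Two design features matter here. Section 2.3.1 admits people "subjectively complaining of stress related to various issues at work". Section 2.4.2 says that "for ethical reasons, the control group will be given InMind for the next 4 weeks".

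**The concern.** The objective is about an effect of MMT, but the planned test estimates the total eight-week change in the treated arm. That total contains any MMT effect plus whatever would have happened anyway: recovery from a stressful period, regression to the mean, shifts in workload, and the effect of answering the same unblinded self-report questionnaires three times. Entry requires a complaint of work stress, so some untreated improvement is plausible, most directly on the PSS.

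The design deals with this at week 4, where the control arm is untreated and is compared directly. At week 8 the controls have also had the app, so no untreated value exists, and the follow-up analysis makes no use of the control arm. Section 2.13 gives no caveat. A significant result would therefore carry the label of a follow-up effect of MMT on evidence that cannot support that label.

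A T1-T3 test does not address maintenance either. It can be significant even when part of the week-4 gain has been lost.

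**Working it through.** **1. The plan's own figure.** Section 2.6 gives effect size 0.15, alpha 0.05, power 0.80, 90 evaluable (45 per group) and 114 recruited (57 per group) after 20% dropout. Read 0.15 as Cohen's f for the 2 × 2 interaction and assume a correlation of 0.5 between time points, which the article does not state:

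- λ = f² × N × m / (1 − ρ) = 0.0225 × 90 × 2 / 0.5 = 8.1
- With 1 and 88 degrees of freedom, power = 0.804; N = 88 gives 0.795.
- Dropout: 45 / 0.8 = 56.25, rounded up to 57 per arm and 114 in total.

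The figure reproduces. It powers the randomised T1-T2 interaction, not the follow-up test.

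**2. The follow-up test when MMT has no effect.** Inputs: n = 57 (recruited) or 45 (evaluable) from section 2.6, and two-sided alpha 0.05. Assumptions: untreated improvement *d* in SD units, and T1-T3 correlation *r*.

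- Standardised paired change: dz = d / √(2(1 − r)). At r = 0.5 this equals d.
- Noncentrality: dz × √n. For d = 0.2, r = 0.5, n = 57: 0.2 × 7.55 = 1.51.
- Chance of a significant result in favour of MMT, from the noncentral t with n − 1 degrees of freedom:

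| Untreated improvement | n = 45, r = 0.5 | n = 57, r = 0.5 | n = 57, r = 0.7 |
|---|---|---|---|
| 0 | 0.025 | 0.025 | 0.025 |
| 0.1 SD | 0.096 | 0.112 | 0.158 |
| 0.2 SD | 0.259 | 0.317 | 0.482 |
| 0.3 SD | 0.503 | 0.605 | 0.820 |

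**3. Five outcomes.** By simulation with n = 45, r = 0.5 and changes on the five scales correlated 0.5 (assumed), at least one of the five tests favours MMT in about 9%, 28%, 58% and 84% of trials for untreated improvements of 0, 0.1, 0.2 and 0.3 SD.

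**4. Is drift of this size conceivable?** Regression to the mean is (1 − r) × the elevation of the baseline score. An assumed elevation of 0.25 to 1.0 SD with r of 0.5 to 0.7 gives between 0.3 × 0.25 = 0.075 SD and 0.5 × 1.0 = 0.50 SD. The elevation is not in the document, so this shows a range and predicts nothing.

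**5. What a concurrent comparator does.** If both arms share the same untreated change, a between-arm test of change scores (45 against 45, simulated) keeps its two-sided error at about 5% for every drift tried from 0 to 0.5 SD. The design offers such a comparator only for T1-T2.

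**6. Can experimental T3 against control T2 replace it?** Adjusted for T1, with n = 57 and r = 0.5, the standard error is √(2(1 − r²)/57) = √(1.5/57) = 0.162 SD. If untreated scores improve by 0.1, 0.2 or 0.3 SD between weeks 4 and 8 and MMT does nothing, this comparison favours MMT in about 9%, 23% or 45% of trials. It removes drift up to week 4 but not drift after it.

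**The case against.** **The hypotheses are within-arm, and the test matches them.** This is true. The mismatch is between those hypotheses and the objective and label above them, which speak of an effect of MMT. The fault therefore lies mainly in what is claimed, and rewording answers most of it. With a four-week wait-list, no analysis can supply an untreated week-8 value.

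**The drift is unknown.** A reader might infer that natural recovery will in fact be reported as an MMT effect. The document does not support that. Section 2.3.1 sets no score cut-off and does not require recent onset, and the Introduction describes work stress as chronic. Elevation on the UWES, CAMS-R or IVS is unknown. What stands is that such change could not be told apart from an effect.

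**The first analysis guards against a useless app.** A reader might infer that an ineffective app would simply be credited with a lasting benefit. But the randomised T1-T2 test would favour an ineffective app in only about 2.5% of trials per outcome, whatever drift the arms share, and a null week-4 result would normally be read beside the paired test. This limits the harm. It does not remove it, because 2.13 does not make the follow-up test conditional on the week-4 result.

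**The Discussion.** It says that "the positive effects of MMT will be maintained even after completing the intervention", which a reader might take as a conclusion drawn from this test. It is not: the text supports that expectation with a cited meta-analysis, and section 3.1 says recruitment has not started.

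**Conclusion.** The point holds as a limit on what the secondary objective can conclude. The planned follow-up test is an uncontrolled pre-post comparison described as an effect of MMT, and week 8 has no untreated arm to compare with. That follows from the text alone and needs no assumption about drift.

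The size does need assumptions. With no MMT effect and r = 0.5, untreated improvement of 0.1 to 0.3 SD would produce a favourable result on a single scale in about 11% to 60% of trials at n = 57, and 10% to 50% at n = 45. These figures are for the paired test taken alone, and neither the drift nor the correlation is stated in the document. It would go too far to say that a false effect will be reported, or that the trial's main conclusion is at risk: the randomised T1-T2 analysis stands as planned.

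**What to change.** - In section 2.13 and in the secondary objective in the Introduction, present the experimental arm's T1-T3 change as descriptive within-arm change, and do not call it an effect of MMT.
- For maintenance, report the experimental arm's T2-T3 change with a confidence interval, beside the randomised T1-T2 group difference.
- State that causal conclusions rest on the T1-T2 comparison only.
- Optionally, add a sensitivity analysis of experimental T3 against control T2, adjusted for T1. State that it is non-concurrent and assumes no untreated change between weeks 4 and 8. For the reason shown in step 6 of the working, it should not become the main follow-up analysis.

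The cost is wording plus one interval per scale, from data already scheduled in Table 2. The downside is a weaker week-8 claim. Recruitment had not started according to section 3.1; if that is still so, the change can be made before any data are seen.

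### The one-arm paired t-test at follow-up is labelled an effect of MMT, but it cannot separate a lasting effect from change that would have occurred without MMT

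*Protocol article*

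**What the plan says.** All references are to the protocol article.

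- **Objective (Introduction).** The secondary objective is given in these words: "perform a follow-up examination to assess the effect of MMT on the mental health, stress, burnout, and work engagement of employees over a longer period". Its five hypotheses share one form, for example "Burnout at follow-up will be lower than that at baseline in the experimental group". No comparator appears in any of them.
- **Test (2.13 Statistical analyses).** A paired t-test is applied to all five scales "in the experimental group to examine the follow-up effect of MMT". The section does not name the two visits; the Introduction shows they are T1 and T3.
- **Controlled analysis (2.13).** The comparison between randomised arms is a "2 (group: experimental vs. control) × 2 (survey time: T1 vs. T2) repeated-measures ANOVA". It stops at week 4.
- **Control arm (2.4.2 Wait-list control).** "The control group will not receive any intervention for the first 4 weeks". After that, "for ethical reasons, the control group will be given InMind for the next 4 weeks".
- **Entry (2.3.1 Inclusion criteria).** "Participants subjectively complaining of stress related to various issues at work". No score threshold is set.
- **Measurement (2.8 Blinding, 2.9 Assessment).** All outcomes are self-reported, and neither participants nor investigators are blinded.
- **Expected reading (3 Discussion).** The authors expect that "the positive effects of MMT will be maintained even after completing the intervention".

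**The concern.** A change from T1 to T3 in one arm is the sum of any effect of MMT and everything else that moves scores over eight weeks: regression to the mean in people who joined while feeling stressed, calendar or workload trends, repeated completion of the same questionnaires, and reporting influenced by knowing one has been trained. The wait-list arm was randomised to remove these influences, and this test does not use it. Even so, the result is named an effect of MMT, and no section restricts it to a descriptive reading.

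The follow-up test is also not made conditional on a positive T1-T2 result. A lasting effect could be claimed on a scale where the randomised comparison showed nothing. The Discussion links favourable results to offering the training at work, so the wording of this conclusion matters.

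**Working it through.** **1. What each comparison can identify**

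| Comparison | Experimental arm | Control arm | Untreated randomised comparator? |
|---|---|---|---|
| T1-T2, group by time | MMT | untreated | yes |
| T1-T3, paired t-test | MMT, then 4 weeks without | not used | no |
| T3, between arms | 4 weeks after MMT | just finished MMT | no |

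The last row shows why a simple between-arm test at T3 does not rescue the objective: both arms have had MMT by then, and the test would compare recent with less recent training.

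**2. The plan's own figure**

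Section 2.6 gives effect size 0.15, alpha 0.05, power 0.80 and a minimum of 90 (45 per group). Read as Cohen's f for the 2 x 2 interaction, with an assumed correlation of 0.5 that the article does not state:

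- noncentrality = f² x N x m / (1 - rho) = 0.0225 x 90 x 2 / 0.5 = 8.1, on 1 and 88 degrees of freedom;
- power = 0.804, and N = 90 is the smallest even total that reaches 0.80.

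With 20% dropout, 45 / 0.8 = 56.25, so 57 per group and 114 in total. The stated figures reproduce. On this reading they support the randomised T1-T2 interaction and say nothing about a controlled claim at T3.

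**3. Behaviour of the paired t-test when MMT does nothing**

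The documents give no untreated drift, so it is treated as unknown and varied. Let d be the mean untreated T1-T3 change in baseline SDs and rho the T1-T3 correlation, with equal SDs at both visits.

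- SD of change = sqrt(2(1 - rho)), which is 1 at rho = 0.5.
- Noncentrality = d x sqrt(n) / SD of change. At n = 45 and rho = 0.5: 0.1 x 6.71 = 0.67; 0.2 x 6.71 = 1.34; 0.3 x 6.71 = 2.01.
- The rejection rate comes from the noncentral t distribution, two-sided 0.05, n - 1 degrees of freedom.

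| Assumed drift (SD) | n = 45, rho 0.5 | n = 57, rho 0.5 | n = 45, rho 0.7 | n = 57, rho 0.7 |
|---|---|---|---|---|
| 0 | 5% | 5% | 5% | 5% |
| 0.1 | 10% | 12% | 14% | 16% |
| 0.2 | 26% | 32% | 40% | 48% |
| 0.3 | 50% | 61% | 72% | 82% |

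These rates are for one scale that drifts by the stated amount.

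**4. The controlled test under the same drift**

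With the same drift in both arms (n = 45 per arm, rho = 0.5, 20,000 simulated trials per setting), the group-by-time test rejected in 5.0%, 4.8%, 5.1% and 5.2% of trials at drifts of 0, 0.2, 0.3 and 0.5 SD. Common drift cancels between arms, so the T1-T2 analysis is protected.

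**5. Precision of a contrast that borrows the control arm's untreated change**

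With equal arms and equal correlations, the standard error of a single mean change is s / sqrt(n), and that of a difference between two independent mean changes is s x sqrt(2 / n). The ratio is sqrt(2), about 1.4.

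**The case against.** The strongest reply has four parts.

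**Drift is not established.** Entry needs only a subjective complaint, with no score cut-off. The scales are first given at T1, so nobody is selected on a baseline score, and people with long-standing stress need not regress. This stands. A reader might infer that scores will improve untreated and that a false lasting effect will be reported. The documents do not support that; they show only that the test could not tell the difference. For the same reason no drift is derived here from a selection formula.

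**Not every scale need be affected.** Entry concerns stress. Burnout, engagement, mindfulness and vitality would be displaced only as far as they relate to the complaint. This also stands. A reader might carry the rates in the table over to all five scales, and nothing in the documents justifies that.

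**The test matches its hypotheses.** The secondary hypotheses are explicitly follow-up against baseline in one arm, and maintenance from T2 to T3 appears only as an expectation in the Discussion. So it would be wrong to say that the plan fails a maintenance objective it set. But the objective above those hypotheses speaks of the effect of MMT, and section 2.13 repeats that label. The mismatch between test and claim remains.

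**Effectiveness is tested with control.** The group-by-time ANOVA answers the primary question. A reader might infer that the trial's main result is undermined; it is not. The problem is confined to the T3 claim.

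**Conclusion.** The point holds for the secondary objective. The plan attributes to MMT a within-arm change that this design cannot attribute, because no untreated randomised comparator exists after week 4 and the chosen test uses no comparator at all. That conclusion follows from the protocol text and needs no numerical assumption.

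The size of the consequence does rest on assumptions. With no drift the test keeps its 5% error rate. With a T1-T3 correlation of 0.5 and 45 participants, a drift of 0.1 SD doubles that to about 10%, and 0.2 to 0.3 SD gives about 26% to 50% for each affected scale. Which row of the table applies cannot be known from the documents. The T1-T2 analysis is unaffected.

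**What to change.** 1. In the Introduction (secondary objective), section 2.13 and the Discussion, describe the experimental arm's T1-T3 change, as an estimate with 95% CI, as a descriptive within-arm change and not as an effect of MMT. Rest causal claims on the T1-T2 group-by-time comparison.
2. As a supporting analysis, report the experimental arm's T2-T3 change with 95% CI as a descriptive indication of maintenance, and say that it is uncontrolled.
3. Optionally, contrast the experimental arm's T1-T3 change with the control arm's untreated T1-T2 change. State that this sets eight weeks against four and assumes no further untreated drift in weeks 5-8.

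**Cost.** All of this uses visits already scheduled and changes only analysis text and wording; the article says recruitment has not started. The follow-up conclusion becomes weaker, and the optional contrast has a standard error about 1.4 times that of the paired comparison. A controlled claim of durability would need a comparator left untreated to T3, which the present wait-list design does not provide.
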